### Ethical approval

Full ethical approval was provided by the Human Research Ethics Committee/08/RPAH/258 (lead committee) of the SSWAHS for protocol No X08-0152 on 10^th ^July 2008 and from local institutional research governance offices for each clinical centre or PI. Written informed consent is obtained for every participant or their parent, carer, guardian or proxy.

## Discussion

Epilepsy is a costly, stigmatized and neglected condition. With the rapidly changing demographic and ethnic makeup of the Australian population, a population-based study of this condition is timely. Through SEISMIC the rates of different epilepsy syndromes, overall and by sex and age group, will be determined for Australia. A feature of this study is its multidisciplinary approach in assessing the impact of epilepsy on individuals, their families and to the community.

SEISMIC will contribute information to promote a healthy life by providing information that will help address the psychosocial and economic impact associated with epilepsy which will ultimately help people live fulfilling and productive lives. The current paucity of prospectively collected population-based Australian data on people with epilepsy hinders the development of programs to reduce this burden. For the first time, data on psychosocial well-being, economic hardship, stigma, and service use following epilepsy will be collected.

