## Background

Currently there is very limited evidence about the burden of epilepsy in the Australian population. The best available estimates based on a cross sectional survey in Tasmania and a study conducted 30 years ago suggest that it is prevalent in between 6 and 7.5 per 1000 people [1,2]. This equates to approximately 150,000 people in Australia presently living with this condition making it one of the 50 leading causes of disease burden and injury in the country [3]. Globally about 50 million people are affected by epilepsy, which accounts for about 1% of days lost to ill health globally [4]. The average incidence across developed countries has been estimated at 43.4/100,000 [5] which would suggest that over 8,800 Australians develop the condition every year. Despite the potential magnitude of the burden of epilepsy, population-based Australian data on the natural history of epilepsy are limited, and strategies to reduce the considerable psychosocial and economic impact of epilepsy are lacking, or poorly understood.

Epilepsy is a chronic neurological disorder with the fundamental characteristic of recurrent, intermittent seizures unprovoked by any acute medical condition or transient brain disorder. A diagnosis of epilepsy is made in those more than 44 weeks post conception, following a second unprovoked seizure occurring at least 24 hours after the first. However "epilepsy" incidence studies have used varying definitions, often including people with single seizures.

Age-specific incidence of epilepsy is bimodal: it is high in those aged over 60 years and highest in children and adolescents, with a slight predominance in males [5,6]. However, it is commonly thought that incidence rates are underestimated in the elderly due to incomplete case ascertainment in studies. Three recent studies have demonstrated a higher incidence in lower income groups in the United Kingdom, New York and Iceland [7-9] and incidence appears to be higher in developing countries [5].

Epilepsy is associated with increased mortality [10], including increased risk of sudden unexpected death (SUDEP) [11], and morbidity: this may be physical (e.g. fractures, scalding, bruising) occurring directly as result of seizures, cognitive (e.g. cognitive delay, speech or language difficulties, learning disabilities), behavioural (e.g. aggression) [12,13], or psychosocial (e.g. depression, anxiety, stigma).

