### Population Base

The population to be surveyed and monitored includes those who are usually resident in the Eastern Zone of the SSWAHS http://www.sswahs.nsw.gov.au. In 2006 the estimated resident population of the SSWAHS was 510,000 people, and comprised 7 local government areas. Children under the age of 15 constitute 16% of the population; people aged 65 years and over make up about 12% and indigenous people comprise 1% of the population. This area is characterized by its multicultural character, with 39% speaking a language other than English at home. Furthermore this population has some of the poorest communities in the State, characterized by a large number of recent migrants, significantly higher unemployment and a high proportion of families dependent on welfare. Overall 40% of the area's population live in rented accommodation. The following hospitals or health-care centres are either in the Eastern Zone of the SSWAHS or treat people with epilepsy who reside within the catchment area: Bankstown Hospital, Brain and Mind Research Institute, Concord Repatriation Hospital, Prince of Wales Hospital, Royal Prince Alfred Hospital, St Vincent's Hospital, Sydney Children's Hospital at Randwick, Westmead including Westmead Children's Hospital. The rooms of private epileptologists, neurologists and paediatricians will also operate as recruiting sites.

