### Statistical considerations

#### Sample size assumption

In the most recent census [52] there were 510,000 people usually resident in the Eastern zone of the SSWAHS. SEISMIC can expect to recruit 254 people with epilepsy per year for a total of 508 over the two year recruitment period. With an estimated 5% refusal, we can expect 484 people to be recruited.

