### Statistical Analysis

The incidence of epilepsy will be reported as definite cases of epilepsy over the population of the study area. Incidence will also be reported by age and syndromic groups. Data analysis will use multivariable one-level (SAS Proc Genmod) as well as mixed model approaches, which take variations within cluster (patients) and between clusters (e.g. hospitals) into account (SAS Proc Mixed). Mixed model approaches will be of use when cluster and individual level data are used to explain a possible outcome, for example, process of care by hospital along with individual level data on language spoken at home as risk factors for adherence to medication.

Multivariable regression will be used to examine the contributions of protective and risk factors on several clinical, psychosocial and economic outcomes. Hypothesised and known risk factors from the literature will be used in the initial regression models, together with factors with a p-value of less than 0.2 in univariate analyses which will be considered as potential confounders. Relative risks and their corresponding 95% confidence intervals will be presented for risk factors as they relate to the outcomes of interest.

Since the length of follow-up for participants will differ depending on the date of diagnosis and hence enrolment into the incident cohort, length of time in the study (and therefore at risk) will be taken into account in regression models. Potential effect modifiers will be examined by inserting interaction terms into the multivariable models.

Survival analyses will be used to investigate the time trajectory of risk and protective factors for various poor outcomes. Kaplan-Meier survival curves will be produced and then the adjusted survival will be examined using Cox proportional hazards models in order to take into account multiple exposure variables.

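### The Discussion promises epilepsy rates for Australia, but the analysis gives only an unstandardised rate for one Sydney zone, and sex is missing from its listed strata

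*Protocol article*

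**What the plan says.** The Discussion makes the national claim: "the rates of different epilepsy syndromes, overall and by sex and age group, will be determined for Australia".

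The Statistical Analysis section defines the measure: "The incidence of epilepsy will be reported as definite cases of epilepsy over the population of the study area". It then adds one breakdown: "Incidence will also be reported by age and syndromic groups". It mentions neither sex-specific incidence nor a standard population.

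The Population Base section restricts the study to "those who are usually resident in the Eastern Zone of the SSWAHS", and the sample size section gives the denominator: "there were 510,000 people usually resident in the Eastern zone of the SSWAHS". On age structure, Population Base says: "Children under the age of 15 constitute 16% of the population; people aged 65 years and over make up about 12" per cent. The same section describes a multicultural area with very poor communities, many recent migrants and raised unemployment.

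The Background states that "Age-specific incidence of epilepsy is bimodal", and that "it is high in those aged over 60 years and highest in children and adolescents, with a slight predominance in males". It also cites three studies that found higher incidence in lower income groups.

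Date of birth and sex are both collected at baseline (Assessments and data collection; Table 1).

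**The concern.** The two sections describe different estimands. The Discussion names a national rate with sex and age strata. The analysis produces a rate for one zone with age and syndrome strata. Nothing stated in the article connects them.

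The gap matters because, on the article's own evidence, incidence depends on features in which a single zone can differ from the country: age, sex and income. A crude rate weights the age-specific rates by the zone's age distribution. Read as a national figure, it carries those weights with it. Syndromes tied to childhood or old age are the most exposed, and syndrome rates are what the Discussion promises.

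National use is also foreseeable. The abstract motivates the study by the scarcity of Australian incidence data, and the Background already converts a rate of 43.4 per 100,000 into a yearly number of new Australian cases.

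**Working it through.** **Side-by-side comparison**

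| Element | Discussion | Statistical Analysis |
|---|---|---|
| Population | Australia | Residents of the study area |
| Overall rate | Yes | Yes, crude |
| By syndrome | Yes | Yes |
| By age | Yes | Yes |
| By sex | Yes | Not listed |
| Step from zone to nation | Implied by the claim | None stated |

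The plan states no incidence figure to reproduce, so the rest only sizes the gap.

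**Implied crude rate and its sampling error**

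Inputs from the sample size section: 254 expected cases per year, 508 over two years, 510,000 residents.

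- Rate = 254 / 510,000 = 49.8 per 100,000 per year.
- Person-years = 2 × 510,000 = 1,020,000.
- Exact Poisson 95% interval for 508 cases: 45.6 to 54.3 per 100,000, or about −8.5% to +9% around the estimate.
- With 443 cases, the number implied by the cited 43.4 per 100,000 (510,000 × 43.4/100,000 × 2 = 443), the interval is 39.5 to 47.7, again about 9% either way.

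**Possible effect of the age mix**

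Formula: standardised/crude = Σ(national share × rate ratio) / Σ(zone share × rate ratio), with ages 15–64 as reference.

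- Zone shares, from Population Base: 16% under 15, about 12% aged 65 or over, so about 72% aged 15–64.
- National shares: not in the documents. Assumed from 14/76/10% to 22/64/14% (under 15 / 15–64 / 65 or over).
- Rate ratios for the young and the old: not in the documents. Assumed from 1.5 to 3.

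| Rate ratio, young and old | Zone index | Index at 14/76/10% | Ratio | Index at 22/64/14% | Ratio |
|---|---|---|---|---|---|
| 1.5 | 0.24 + 0.72 + 0.18 = 1.14 | 0.21 + 0.76 + 0.15 = 1.12 | 0.98 | 0.33 + 0.64 + 0.21 = 1.18 | 1.04 |
| 3 | 0.48 + 0.72 + 0.36 = 1.56 | 0.42 + 0.76 + 0.30 = 1.48 | 0.95 | 0.66 + 0.64 + 0.42 = 1.72 | 1.10 |

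A crude 49.8 per 100,000 would become about 47 (49.8 × 0.949 = 47.2) to 55 (49.8 × 1.103 = 54.9). The ratio crosses 1, so even the sign depends on the assumed national age mix.

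**Extreme case for a single syndrome**

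If a syndrome occurred only under age 15, the rate ratios would drop out and the ratio would be national share / 16%. Under the same assumed shares this is 14/16 = 0.88 to 22/16 = 1.38. Again the sign is open, but the possible shift is larger than for the overall rate.

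**What age and sex cannot reach**

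The income gradient in the Background, together with the deprivation described in Population Base, could raise the zone's rate above the national one within every age and sex group. Reweighting by age and sex leaves that difference untouched, and the documents give nothing from which to size it.

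**The case against.** The strongest reply is that this is a condensed article. It gives incidence two sentences, and the choice of standard population is the sort of detail usually left to a full protocol or analysis plan. The planned age-specific rates already supply the main input for standardisation, and the text does not rule it out. The planned rate is also openly described as belonging to the study area. Much of this stands: missing standardisation, taken alone, would not be a finding. The Discussion's claim is different, because it commits to a national result that the stated analysis does not deliver.

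Three stronger readings are tempting and should be resisted:

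- A reader might infer that the headline rate is biased, and biased downwards because the zone has relatively few children and older people. The documents do not support this. The crude rate is a correct measure for the zone. Error arises only if it is read as national, and its direction needs a national age mix that the documents do not give. The income gradient could push the other way.
- A reader might infer that sex-specific rates are not planned. The Discussion announces them and sex is collected. The analysis section omits sex from a short list; it does not exclude it.
- A reader might infer that the study's rate will be set against 43.4 per 100,000. That figure appears only as background, and no such comparison is planned.

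**Conclusion.** The point holds as a mismatch between a national claim and a zone-level analysis, with a second, smaller mismatch over sex. Followed as written, the plan would attach a crude zone rate to a conclusion about Australia that it does not support.

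The size is conditional. The range of about 0.95 to 1.10 for the overall rate rests entirely on the assumed national shares and rate ratios. It is comparable to the sampling error but, unlike that error, would not shrink with more cases. The socioeconomic component is unquantified.

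Severity is low. The primary aim concerns modifiable factors behind the socioeconomic impact of epilepsy, and nothing here touches it.

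**What to change.** **Statistical Analysis.** Add that overall and syndrome-specific incidence will be directly standardised by age and sex to the national population, and reported beside the crude rates and the age-by-sex-specific rates. Listing sex among the strata removes the second mismatch whichever way the first is settled. The edition of the standard population and the age bands can be left to the analysis plan.

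**Discussion.** Limit the claim either to the study area or to the age- and sex-standardised rate. In the second case, state that standardisation does not remove the zone's socioeconomic and migrant differences from the rest of the country, so the figure is a national estimate only if rates within each age and sex group are similar.

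**Cost.** One more table from data already collected, and slightly wider intervals for the standardised rates than for the crude ones. Recruitment, assessments and the primary analysis do not change.
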